## Standard of care framework

Irrespective of group allocation, all participants receive the institutional standard multimodal anesthesia and analgesia protocol, which is managed by the Acute Pain Service. Intraoperatively, all patients undergo a standardized general anesthesia regimen, including continuous hemodynamic monitoring (5-lead electrocardiogram, pulse oximetry, non-invasive and invasive arterial blood pressure) and controlled mechanical ventilation. Crucially, to provide preventive analgesia and mitigate the neuroendocrine stress response associated with major surgical trauma, early analgesic interventions—incorporating regional techniques such as thoracic epidural placement (T5-T12) or fascial plane blocks, tailored to the specific surgical approach—are systematically performed immediately following anesthetic induction and prior to the surgical incision. Postoperatively, this regimen employs a balanced strategy integrating peripheral analgesics, nonsteroidal anti-inflammatory drugs, and targeted opioid administration. In the immediate postoperative phase, pain is controlled through intravenous morphine titration, consisting of 2 mg boluses administered every 5 to 10 min until a Visual Analogue Scale score below 3 is achieved.

Subsequently, analgesic maintenance is provided via Patient-Controlled Analgesia pumps. These devices utilize a standardized 0.5 mg/ml morphine solution, programmed for demand boluses of 0.5 to 1.0 mg with a 7 to 15 min lockout interval. Furthermore, pain intensity is systematically evaluated as a vital sign during routine hemodynamic checks utilizing the Visual Analogue Scale (VAS). Concurrently, the Richmond Agitation-Sedation Scale (RASS) is monitored by the ICU clinical team as a safety and eligibility parameter. To ensure protocol fidelity and patient safety, a Virtual Reality session is only initiated if the patient is in an optimal state of alertness, defined as a RASS score between −1 (drowsy) and +1 (restless). Patients presenting with severe agitation (RASS ≥ +2) or deep sedation (RASS ≤ −2) will have their sessions postponed until clinical stabilization. Consequently, the uniform application of this baseline framework across all study arms ensures that any variations in cumulative opioid consumption can be attributed directly to the digital interventions being investigated.

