Conversely, the exclusion criteria are systematically applied and scientifically justified to ensure patient safety and protocol fidelity:•**Clinical and Operational Status:** Patients currently requiring invasive mechanical ventilation at the time of the scheduled intervention (due to physical interference with the VR headset and inability to interact), or those presenting with active infectious-contagious diseases. Recent surgical trials dictate that these exclusions are critical, as such clinical states limit the required active cooperation, pose risks of device displacement, and significantly increase the likelihood of cross-contamination with head-mounted displays [18].•**Cognitive and Neurological Baseline:** Patients with a documented cognitive deficiency, defined by a Mini-Mental State Examination (MMSE) score of 24 or lower, as well as those diagnosed with other cognitive disorders or spatial orientation deficiency. This specific cutoff is supported by Cochrane systematic reviews, which demonstrate that an MMSE score of 24 provides an optimal balance of 85% sensitivity and 90% specificity for detecting cognitive impairment, thereby preventing the inclusion of individuals unable to fully comprehend instructions or interact with complex virtual environments [19].•**Physical and Sensory Constraints:** Individuals with sensory or physical limitations, specifically severe visual impairments and upper limb motor deficits. This exclusion guarantees that patients possess the physical ability to safely interact with the hardware and fully perceive the virtual environment.•**Psychological and Vestibular Intolerance:** Conditions that directly contraindicate immersive technologies, notably claustrophobia and motion sickness, including labyrinthine diseases. While recent meta-analyses confirm that virtual reality is generally safe, mild adverse events such as nausea, dizziness, and cybersickness are still reported, with some clinical trials noting dropout rates of up to 13% due to these symptoms, making the exclusion of highly susceptible populations essential to guarantee patient safety and maintain strict protocol adherence [20].

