## Virtual reality interventions

For the intervention arms, a progressive additive model is applied to ensure clear methodological differentiation. Group 3 serves as the control and receives the institutional standard multimodal anesthesia and analgesia protocol. To maintain high external validity and reflect real-world intensive care conditions, pharmacological management and rescue analgesia for all groups are strictly governed by the institutional Standard Operating Procedure for Acute Pain Management. According to this protocol, pain is objectively assessed during every routine vital sign check. Adequate pain control is institutionally defined as a Visual Analogue Scale (VAS) score of 3 or less. Consequently, subjective bedside dosing is minimized, as any reported pain score of VAS ≥ 4 (categorized as moderate to severe pain) triggers mandatory re-evaluation and the administration of standardized rescue interventions—including oral, intermittent intravenous, or PCA titrations—until the target of VAS < 3 is achieved. Furthermore, to preserve the pragmatic nature of the trial, participants in the control group are not restricted from using standard non-immersive personal devices, such as smartphones or hospital televisions. Restricting access to these devices is considered ethically and logistically inviable due to the essential need for family communication during a critical postoperative period and the inherent setup of shared hospital rooms. Therefore, this study is pragmatically designed to evaluate the supplementary efficacy of virtual reality immersion against the baseline noise and unstructured digital distractions that already constitute the real-world standard of care. This methodological allowance is further grounded in the premise that the therapeutic mechanism of virtual reality relies on multisensory immersion, which fundamentally differs from the limited cognitive engagement provided by conventional two-dimensional screens.

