## Trial procedures and data collection

The protocol begins in the preoperative phase with a systematic cognitive screening applied to all potential participants. Specifically, the Mini-Mental State Examination (MMSE) is administered to every patient prior to surgery, including those subsequently randomized to the control group, to ensure a baseline of cognitive function that is homogeneous across the entire cohort. Furthermore, once clinically stabilized after surgery and extubated in the ICU, randomized patients start their assigned VR sessions from the first to the fifth postoperative day. The target duration for each session is 45 min to maximize the immersive analgesic effect. However, to prioritize patient comfort and mitigate visual fatigue, the protocol permits a voluntary early cessation at 30 min based on spontaneous patient requests, thereby defining the 30 to 45 min therapeutic window. These sessions are performed three times daily. The total cumulative time of hardware exposure is recorded for each participant to ensure a standardized evaluation of the immersive therapeutic dose across all intervention groups. Specifically, this therapeutic dose will be analyzed as a continuous variable, calculated by summing the total minutes across all 15 sessions. Early interruptions are not classified as protocol deviations, but rather as expected natural fluctuations in patient tolerance, being appropriately captured as a lower cumulative dose within the Intention-to-Treat (ITT) framework.

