To preserve the integrity of the initial randomization sequence while avoiding the imputation of an entire evaluation period for early dropouts, the primary efficacy analysis will be conducted adhering to a modified Intention-to-Treat (mITT) principle. This approach encompasses all randomized participants who received the allocated intervention and underwent at least one post-randomization clinical assessment. To handle potential missing longitudinal data resulting from early clinical discharge, severe postoperative complications, or protocol non-adherence, the analysis will rely on the inherent capacity of the GLMM to manage missing observations under the Missing at Random (MAR) assumption. Additionally, to account for data that may be Missing Not at Random (MNAR)—particularly due to asymmetric dropout rates driven by intervention-related adverse effects such as cybersickness—a sensitivity analysis utilizing Pattern-Mixture Models will be conducted to assess the robustness of the primary findings. Furthermore, a secondary per-protocol analysis will be performed for participants who completed a minimum of two therapeutic sessions per day to evaluate the intervention’s efficacy under optimal adherence conditions. A standard significance level of p < 0.05 will be established. Finally, the statistician performing the final data analysis will be blinded to the group allocation codes.

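### The primary modified ITT set requires receipt of the allocated intervention, a condition only the two VR arms can realistically fail, so it does not preserve randomization and can bias the opioid comparison

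*Protocol article*

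**What the plan says.** The Statistical analysis plan section defines the set for the primary efficacy analysis as follows: "This approach encompasses all randomized participants who received the allocated intervention and underwent at least one post-randomization clinical assessment". It gives two reasons: keeping the randomization intact, and "avoiding the imputation of an entire evaluation period for early dropouts". The same section adds a pattern-mixture sensitivity analysis for data missing not at random, and a per-protocol analysis of patients with at least two sessions a day. It names no analysis of all randomized patients.

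Four other places bear on who can fail the receipt condition:

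- Virtual reality interventions: "Group 3 serves as the control and receives the institutional standard multimodal anesthesia and analgesia protocol".
- Standard of care framework: whatever the allocation, "all participants receive the institutional standard multimodal anesthesia and analgesia protocol". This section also postpones a VR session when the RASS score lies outside -1 to +1.
- Trial procedures and data collection: "once clinically stabilized after surgery and extubated in the ICU, randomized patients start their assigned VR sessions". On sessions cut short, it describes them as "being appropriately captured as a lower cumulative dose within the Intention-to-Treat (ITT) framework".
- Sample size and study population, among the exclusions: "Patients currently requiring invasive mechanical ventilation at the time of the scheduled intervention".

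The primary endpoint is postoperative MME, taken from pump logs and medical records (Clinical endpoints and blinding; Limitations) and divided by each patient's own observation time (Statistical analysis plan).

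**The concern.** A control patient is allocated nothing beyond standard care, and everyone gets standard care, so a control patient cannot realistically fail the receipt condition. A VR patient can, by never reaching a first session: prolonged ventilation, a RASS score that stays outside the window, instability, or refusal of the headset. The same kinds of patient exist in the control arm and are kept there.

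Membership of the primary set thus depends on something that happens after allocation and operates in two arms of three. Randomization no longer guarantees that the groups compared are alike. At stake is the MME comparison, which is tested at p < 0.05 and is meant to inform later definitive trials. The pattern-mixture models deal with missing values among analysed patients and do not bring excluded patients back. The per-protocol analysis restricts further.

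**Working it through.** **Does the plan have a figure to reproduce?** No. There is no power calculation and no expected number of non-starters. The only related figure is the sample size, and it is consistent: 20 blocks × 3 = 60 = 3 arms × 20.

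**Inputs.** From the protocol: 20 patients per arm, 1:1:1 allocation, significance level 0.05. Assumed, because the documents give neither: the fraction f of each arm that would never start VR, and the opioid use of those patients relative to the rest.

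**Step 1: relative shift with no true effect.** Set the mean MME rate of a whole arm to 1. If the non-starters average r, the starters average (1 - f·r)/(1 - f). The control arm keeps everyone and stays at 1. The shift in the VR mean is therefore

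(1 - f·r)/(1 - f) - 1 = f(1 - r)/(1 - f).

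| f | r | Calculation | Shift in VR mean |
|---|---|---|---|
| 5% | 1.5 | -0.025/0.95 | -2.6% |
| 10% | 1.5 | -0.05/0.90 | -5.6% |
| 10% | 2 | -0.10/0.90 | -11% |
| 15% | 2 | -0.15/0.85 | -18% |
| any | 1 | 0 | 0 |
| 10% | 0.5 | +0.05/0.90 | +5.6% |

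Negative values favour VR. The sign depends only on whether r is above or below 1.

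**Step 2: the same in standard deviations.** If non-starters differ from starters by d SD, the VR mean is that of the starters and the control mean is higher by f·d. VR minus control is -f·d. For f = 10% this runs from +0.05 SD (d = -0.5) to -0.15 SD (d = +1.5); for f = 20%, from +0.10 to -0.30 SD.

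**Step 3: chance of a false significant result favouring VR.** This was simulated with 20,000 runs per scenario, normal outcomes, both VR arms pooled (40) against control (20), and a t-test at two-sided 0.05. The test is a simplification of the planned mixed model, and two-sidedness is assumed. The nominal value is 2.5%.

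| f | d = -0.5 | d = 0 | d = +0.5 | d = +1.0 | d = +1.5 |
|---|---|---|---|---|---|
| 5% | 2.0% | 2.6% | 3.1% | 3.9% | 4.3% |
| 10% | 1.7% | 2.3% | 3.6% | 5.3% | 7.5% |
| 20% | 1.1% | 2.4% | 5.1% | 10.3% | 16.1% |

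With all randomized patients analysed as allocated, the same runs gave 2.2% to 2.7% in every scenario. At f = 10%, the rule removes on average 2 of 20 patients from each VR arm and none from control.

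**Step 4: does the stated reason require the exclusion?** A non-starter who is still under observation has a pump log and a chart, so MME is recorded without any VR session. Division by the patient's own observation time gives a rate even when follow-up is short. For these patients there is no evaluation period to impute.

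**The case against.** **Few patients may be lost.** A postponed session is not cancelled, up to 15 are offered over five days, and a patient must miss all of them to be dropped. Someone who stops after one session, for example with cybersickness, has presumably received the intervention and stays in. Patients are 16 to 40 years old and enrol because VR interests them, and all three pilot patients completed at least two of three daily sessions. This stands as a limit on size: f could be near zero, though three patients are weak evidence. It does not make the rule symmetric.

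**A reader might infer that the rule biases the result toward VR because the sickest, highest-opioid patients leave.** The documents report no opioid use for non-starters. Patients with low need may decline the headset or go home before a first session, and deeply sedated patients on demand-bolus analgesia need not be high consumers. The direction is plausible but not established.

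**A reader might infer that the ventilation exclusion acts after allocation.** The protocol says that the arm is revealed after consent and enrolment, but does not place this relative to surgery or extubation. If envelopes are opened after extubation, that route closes. It remains a possibility only.

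**A reader might see opposing rules in the two ITT statements.** The sentence under Trial procedures concerns sessions cut short. Those patients have started VR and are kept under the modified rule too, so this is loose labelling and not a conflict of rules.

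**The trial is a proof of concept.** True, and no power claim is broken by losing a few patients. But a preliminary signal still needs a comparison that randomization protects.

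The condition of at least one post-randomization assessment applies to all arms and is not part of this point.

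**Conclusion.** The point holds for the definition of the primary set. The receipt condition is applied after randomization, can realistically be failed only in the VR arms, and contradicts the stated aim of keeping the randomization intact. Nothing else named in the plan restores the excluded patients.

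The size and sign of the bias are conditional. For f of 5% to 15% and r of 1.5 to 2, the VR mean falls by about 2.6% to 18% with no true effect. At r = 1 there is no shift, and below 1 it runs against VR. These results rest on assumed values of f and r, and on the non-starters being alike in every arm. Confidence is high in the asymmetry, and much lower in direction and size.

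**What to change.** 1. Define the primary analysis set as all randomized patients in their assigned arm, whether or not any VR session took place, using MME from pump logs and charts over each patient's observation time.
2. Keep the receipt-based set as a sensitivity analysis, described as such.
3. In the Statistical analysis plan section, remove the claim that the receipt-based set keeps the randomization intact, and the imputation argument as applied to patients who are still observed. Align the ITT label under Trial procedures and data collection with the new definition.

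This costs wording only, because the primary endpoint is already collected from sources that do not depend on VR use. The downside is slight dilution. If non-starters gain nothing from VR, the estimated effect is (1 - f) times that among starters, for example 0.90 times at f = 10%.

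Delaying the opening of envelopes until patients are ready for VR is not recommended. It could place early postoperative opioid use before randomization, and so alter the endpoint window and the enrolled population. It is largely unnecessary once everyone randomized is analysed.

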Consequently, patient safety was quantitatively validated throughout the entire pilot period by continuously monitoring vital signs, including heart rate, mean arterial pressure, oxygen saturation, and respiratory rate, alongside tracking signs of cybersickness. In these preliminary assessments, patients within the targeted age group of 16 to 40 years reported high levels of comfort and ease of use with the hand tracking features in the First Hand and Oculus First Contact applications. Across the 45 executed sessions, the incidence of adverse events was limited to a single report of mild dizziness. While this represents an occurrence rate of 33.3% at the patient level (1 out of 3 patients), when analyzed by total therapeutic exposure, the adverse event occurred in only 1 out of the 45 sessions (a 2.2% per-session rate). Although this preliminary sample is too small to draw definitive conclusions regarding overall clinical safety, these pilot results confirmed the initial technical feasibility and general tolerability of the repeated-exposure protocol, allowing the main trial to proceed.

Moreover, the adherence rate was formally assessed, demonstrating that all the participants were able to successfully complete at least two of the three daily sessions, thereby meeting the minimum threshold established for inclusion in the final data analysis.

Finally, the data collection infrastructure was validated through a mock entry process using the REDCap platform. This procedure ensured that all clinical variables, particularly the Visual Analogue Scale (VAS) scores and precise opioid dosages extracted from patient-controlled analgesia (PCA) pumps, are accurately captured, synchronized, and ready for subsequent statistical analysis.

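### The secondary per-protocol rule of two sessions per day has no counterpart for controls, and one sentence words it as the entry threshold for the final analysis

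*Protocol article*

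**What the plan says.** The Statistical analysis plan section makes the primary efficacy analysis mITT: randomized patients who received what they were allocated and had at least one assessment afterwards. It sets no number of sessions per day. It then adds that "a secondary per-protocol analysis will be performed for participants who completed a minimum of two therapeutic sessions per day", in order to estimate "efficacy under optimal adherence conditions". No arm is named, and no adherence criterion is given for controls.

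The Virtual reality interventions section says that "Group 3 serves as the control and receives the institutional standard multimodal anesthesia and analgesia protocol". Sessions belong to the VR arms: under Trial procedures and data collection, "randomized patients start their assigned VR sessions from the first to the fifth postoperative day", and "These sessions are performed three times daily".

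The same section says that "Early interruptions are not classified as protocol deviations" and keeps the reduced exposure in the intention-to-treat analysis as a lower dose. Dose is a continuous variable, "calculated by summing the total minutes across all 15 sessions".

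The Protocol validation section reports that every pilot patient managed at least two of the three daily sessions, "thereby meeting the minimum threshold established for inclusion in the final data analysis".

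**The concern.** There are two problems and one smaller consequence.

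**One-sided rule.** A criterion that counts VR sessions cannot be met by patients who are offered none. Read literally, the per-protocol set has no controls. If all controls are kept and only VR patients are filtered, the comparison is no longer between randomized groups. The article itself treats session completion as dependent on the patient's condition. Sessions are postponed for agitation or deep sedation (Standard of care framework), symptom-related dropout of up to 13% is cited (exclusion criteria), and dropout from cybersickness is expected to differ between arms (Statistical analysis plan). That sedation, nausea and complications also go with opioid use is an inference, but a reasonable one. The retained VR patients would then tend to need less opioid even if the headset did nothing.

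**Conflicting statements of who is analysed.** The validation section words the threshold as a condition for the final analysis; the analysis section has no such condition for its primary set.

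**Dose.** The opioid outcome is divided by observation time because stays differ, but the dose is a plain sum over 15 sessions. If that sum is used as an exposure measure, it partly reflects length of stay.

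**Working it through.** **Session counts.** 3 per day × 5 days = 15 sessions; 15 × 45 min = 675 min = 11.25 h; 3 pilot patients × 15 = 45 sessions. All agree with the article. Over five full days the rule needs at least 2 × 5 = 10 of 15 sessions, with two on every day.

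**Who qualifies.**
- Controls: 0 sessions by design, so 0 of 20.
- VR patients: the article gives no adherence figure for the trial. Assume each session is completed independently with probability q. The chance of two or more in a day is 3q²(1−q) + q³, raised to the fifth power for five days.

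| q (assumed) | one day | all five days | of 20 |
|---|---|---|---|
| 0.95 | 0.993 | 0.964 | 19.3 |
| 0.90 | 0.972 | 0.868 | 17.4 |
| 0.85 | 0.939 | 0.731 | 14.6 |
| 0.80 | 0.896 | 0.577 | 11.5 |

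Retention of 60–80% is therefore plausible but not established. The pilot does not settle it: 3 of 3 adherent gives an exact two-sided 95% lower limit of 0.025^(1/3) = 0.29.

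**Size of the selection shift.** Assume no treatment effect, all controls kept, a share p of VR patients kept, and correlation ρ between adherence and low opioid need, with both normally distributed. The retained VR mean lies below the control mean by ρ × φ(z)/p SD, where z cuts off the lower 1 − p of the adherence distribution. For p = 0.8, φ(z)/p = 0.350, so ρ = 0.3 gives 0.105. For p = 0.6, φ(z)/p = 0.644, so ρ = 0.5 gives 0.322.

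A simulation of 40,000 null trials per cell (40 pooled VR patients before filtering, 20 controls, two-sided t-test at 0.05) gave the false-positive rates below. Its mean shifts agreed with the formula.

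| share kept | shift, ρ = 0.3 | shift, ρ = 0.5 | false positives, ρ = 0.3 | false positives, ρ = 0.5 |
|---|---|---|---|---|
| 0.9 | 0.058 | 0.097 | 5.4% | 6.6% |
| 0.8 | 0.105 | 0.175 | 6.5% | 9.8% |
| 0.7 | 0.149 | 0.248 | 8.2% | 14.3% |
| 0.6 | 0.193 | 0.322 | 10.0% | 19.2% |

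The shift favours VR in every cell. The t-test stands in for the planned mixed model, so the rates are illustrative.

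**The texts side by side.** A VR patient who completes one session a day and has a postoperative assessment is in the mITT set. Under the validation sentence the same patient is outside the final analysis. Both cannot hold.

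**The case against.** The strongest reply is that the primary result is not at risk. The article calls the per-protocol analysis secondary and frames all results as preliminary signals, and selection after randomization is a known weakness of any per-protocol set. This stands and limits the severity.

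A reader might infer from the validation sentence that the main analysis is restricted to adherent patients. The article does not support that. The sentence reports pilot adherence, and the only two-session threshold in the analysis section is the secondary one, so loose wording is the likelier explanation. The sentence still needs correcting.

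A reader might also infer that the rule fails for every contrast. It does not: for Group 1 against Group 2, a stated aim, it applies equally to both arms, although the two arms may still retain different kinds of patient. Nor would an inert headset necessarily appear to work. Within the assumed range of 60–80% retained, the false-positive rate is 6.5–19.2%, so most null trials would still be non-significant. With most VR patients retained, the subset is better-tolerating rather than only the best.

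The sentence on early interruptions mainly concerns stopping a session short, so it conflicts with the validation wording in principle more than in letter. The 15-session sum remains a valid record of total exposure, and the article states no model of outcome on dose; that point matters only if dose is analysed.

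A fuller plan might say how controls enter the per-protocol set. But the article already fixes the criterion and its purpose, and letting all controls in would leave the selection in place.

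**Conclusion.** The point holds as a moderate one about a secondary analysis. That controls cannot meet the rule follows directly from the text. A VR-versus-control per-protocol contrast is therefore either empty on one side or biased towards VR. The size, about 0.10–0.32 SD, rests wholly on assumed retention of 60–80% and an assumed correlation of 0.3–0.5; it falls to about 0.06–0.10 SD at 90% retention. It should not be scaled against the standardized effect of −0.65 that the article cites: that is an overall analgesic effect, and the article itself declines to carry such figures into this population.

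The conflict between the validation sentence and the mITT definition is certain as text. Its effect on the primary result is not shown.

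**What to change.** 1. In Protocol validation, say that two sessions per day defines only the secondary per-protocol set, and that the primary mITT analysis has no daily session minimum.
2. Report the two-session subset descriptively within the VR arms, with no p-value against control. Say how the daily count works for patients discharged before day five.
3. If dose is analysed, express it as minutes per available session or per inpatient day, to match the opioid rate per 24 h.
4. Optionally, add an exploratory complier-average estimate in all randomized patients, with allocation as the instrument. State that it assumes allocation acts only through VR exposure, which the attention and expectancy effects acknowledged under Limitations may violate, and that its interval will be wide at 20 per arm.

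Items 1 to 3 cost wording and a simple recalculation, with no change to recruitment or conduct. The price is giving up a formal VR-versus-control test under good adherence, which the rule as written could not deliver without bias. Item 4 costs one extra model.
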